#### 4. Study Design

##### 4.1. Overview of Study Design

Intervention Model: Single-group

Control: Baseline control

Active Comparator: None

Allocation Method: None

Masking: None

Target Population Type: Adult subjects

Target Population Diagnosis: SMH secondary to AMD or RAM

Target Population Age Range: Minimum 18 years, no upper limit

Distribution of Study Sites: Multicenter collaborative

Trial Phase: Phase II

Committee: None

Duration of Participation per Subject: 12-week observation period after enrollment

#### 4.2. Rationale for Study Design

##### <Single-Group Trial>

The natural course of SMH varies according to hematoma volume and location of bleeding. Small hematomas or hemorrhages that do not involve the fovea may resolve spontaneously with minimal impact on visual acuity. In this study, we will enroll severe patients in whom a large hematoma is unlikely to resolve spontaneously and whose bleeding involves the fovea, resulting in a predicted marked loss of visual acuity. The study will therefore be a pre-post comparison trial evaluating objective measurements reflecting hematoma volume and visual function before and after tPA administration. In the patient population targeted by this trial, improvement of the disease state is not expected with no treatment, vitrectomy with gas tamponade, or vitrectomy with oil tamponade; consequently, establishing a control arm would be ethically unacceptable. Moreover, sub-retinal administration of a placebo could cause complications such as retinal detachment, rendering a placebo arm ethically unacceptable. Accordingly, the trial will be conducted without a control group as an open-label, single-arm study of the investigational product.

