## <Estimand for the Primary Objective>

Primary clinical question: In patients with SMH due to AMD or RAM, regardless of the use of VEGF-inhibitor therapy or the use of tPA formulations for other diseases, what is the change in central foveal hemorrhage volume at the 1-week time point after subretinal administration of montepilase (recombinant)?

|                                    |                                                                                                                                                                                                                 |
|------------------------------------|-----------------------------------------------------------------------------------------------------------------------------------------------------------------------------------------------------------------|
| i. Treatment condition of interest | Subretinal administration of montepilase (recombinant)                                                                                                                                                          |
| ii. Population                     | Patients with SMH defined by the inclusion criteria (severe sub-macular hemorrhage in which spontaneous resolution is not expected, the bleed involves the fovea, and marked visual-acuity loss is anticipated) |
| iii. Endpoint                      | Change from baseline to week 1 in CFT measured by optical coherence tomography (OCT)                                                                                                                            |
| iv. Other intercurrent events      | See Table 3-1                                                                                                                                                                                                   |
| v. Population-level summary        | Mean change from baseline to week 1 in CFT                                                                                                                                                                      |

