##### <Target Population>

Patients whose underlying disease is AMD or RAM, the principal causes of SMH, will be eligible. Considering the invasiveness and risk of sub-retinal administration, only patients with at least moderate severity will be enrolled: those with a CFT  $\geq 300 \mu\text{m}$  and a BCVA  $\leq 0.2$  (decimal). Patients in whom the clot is organized and unlikely to dissolve, those with concomitant ocular diseases that could affect efficacy or safety assessments, and those at high risk of further bleeding will be excluded.

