#### 5.1. Inclusion Criteria

Subjects are eligible to participate in this trial only if they meet all of the following criteria:

Age:

- 1) Patient aged  $\geq 18$  years at the time of signing the informed consent form.

Disease Characteristics:

- 2) Patient with sub-macular hemorrhage involving the fovea secondary to AMD or RAM in the study eye.

- 3) At screening, CFT measured by OCT in the study eye is  $\geq 300 \mu\text{m}$ .
- 4) At screening, BCVA in the study eye is  $\leq 0.2$  (decimal).

Other:

- 5) Patient who can provide written informed consent; if visual impairment makes document review difficult, verbal consent may be obtained from the subject together with the signature of a witness.
- 6) (For women of child-bearing potential) Patient who, from the time informed consent is obtained until 2 days after investigational product administration, agrees to use an appropriate method of contraception\*.

\* See 10.3.2.

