### 8.2.2. Fundus Photography (both eyes)

Under pharmacologic dilation, capture fundus photographs and assess for the presence of a

central foveal hemorrhage  $\geq$  one optic-disc diameter, as well as for marked organization or fibrosis of the hemorrhage. Document any other abnormalities in detail in the case report form.

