### 9.4. Analyses Supporting Secondary Objectives

#### 9.4.1. Analyses Supporting Secondary Objectives

##### 1) Change from baseline in CFT at week 4

For CFT, the 95 % confidence interval of the mean change from baseline at week 4 will be calculated, and a significance test will be performed using a t-test.

##### 2) Presence of a foveal hemorrhage $\geq 1$ disc diameter at week 4

The proportion of subjects with a foveal hemorrhage  $\geq 1$  disc diameter at week 4 will be evaluated for significance using a chi-square test.

##### 3) BCVA (logMAR equivalent) at week 4

For BCVA (logMAR equivalent), the 95 % confidence interval of the mean at week 4 will be calculated.

##### 4) Change from baseline in BCVA (logMAR equivalent) at week 4

For BCVA (logMAR equivalent), the 95 % confidence interval of the mean change from baseline at week 4 will be calculated, and significance will be tested using a t-test.

##### 5) Change from baseline in CFT at week 12

For CFT at week 12, the 95 % confidence interval of the mean change from baseline will be calculated, and significance will be tested using a t-test.

##### 6) BCVA (logMAR equivalent) at week 12

For BCVA (logMAR equivalent), the 95 % confidence interval of the mean at week 12 will be calculated.

##### 7) Change from baseline in BCVA (logMAR equivalent) at week 12

For BCVA (logMAR equivalent), the 95 % confidence interval of the mean change from baseline at week 12 will be calculated, and significance will be tested using a t-test.

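### Secondary endpoint 2 counts an eye that never had a foveal hemorrhage of 1 disc diameter as free of one at Week 4, because no eligibility criterion sets lateral extent

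*Protocol*

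**What the plan says.** **Population.** The single-group rationale in section 4.2 begins with natural history: "Small hematomas or hemorrhages that do not involve the fovea may resolve spontaneously with minimal impact on visual acuity". It then states that "we will enroll severe patients in whom a large hematoma is unlikely to resolve spontaneously and whose bleeding involves the fovea", and argues against a control arm because in this population "improvement of the disease state is not expected with no treatment, vitrectomy with gas tamponade, or vitrectomy with oil tamponade". The target-population paragraph of the same section uses a different grade: "only patients with at least moderate severity will be enrolled", which it defines by CFT and BCVA. In section 3 the primary estimand ties its population to the inclusion criteria and describes it as "severe sub-macular hemorrhage in which spontaneous resolution is not expected, the bleed involves the fovea, and marked visual-acuity loss is anticipated". Both secondary estimands repeat this.

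**Eligibility.** In section 5.1, criterion 2 reads "Patient with sub-macular hemorrhage involving the fovea secondary to AMD or RAM in the study eye". Criteria 3 and 4 add CFT of at least 300 µm and decimal BCVA of at most 0.2. Neither section 5.1 nor section 5.2 contains a limit in disc diameters, area or volume.

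**Endpoint.** For the Week 4 hemorrhage endpoint, section 3 fixes the summary measure as a proportion of patients. Section 9.4.1, item 2, tests "The proportion of subjects with a foveal hemorrhage" of 1 disc diameter or more at Week 4 with a chi-square test. Neither place conditions on baseline, and the FAS definition in section 9.2 adds no such condition.

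**Data.** Section 8.2.2 instructs: "Under pharmacologic dilation, capture fundus photographs and assess for the presence of a" foveal hemorrhage of at least one disc diameter. The schedule in section 1.3 places fundus photography at screening as well as at Week 4.

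**The concern.** A Week 4 proportion shows what happened to hemorrhages of at least 1 disc diameter only if the subjects had one at the start. The criteria do not ensure this. Subjects who enter below that extent fall into the favourable category from the outset, so the result mixes response with the composition of the sample at entry. The artefact runs in the favourable direction, and there is no control arm in which it would cancel.

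The same missing criterion exposes a mismatch in the text. The no-control rationale speaks of large hematomas, the target-population paragraph of at least moderate severity, and the estimand of bleeds not expected to resolve. The criteria select on location, foveal thickness and acuity. A reader of the results needs to know which of these populations was studied.

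**Working it through.** **1. The plan's own figure.** Section 9.9 gives 19 subjects, raised to 20. Exact noncentral-t power for a one-sample, two-sided 5% test with effect size 0.70 is 0.799 at n = 18 and 0.823 at n = 19, so 19 is reproduced. Then 19 / 0.95 = 20. This calculation concerns Week 1 CFT change and does not depend on hemorrhage extent, so the point leaves it untouched.

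**2. Does the CFT criterion imply extent?** Section 3 defines CFT as retina plus hemorrhage at the fovea and says that it also captures hemorrhagic PED. It is a thickness at one location. If the retina is assumed to contribute 200 to 275 µm (the protocol gives no figure), a CFT of exactly 300 µm leaves 300 − 275 = 25 to 300 − 200 = 100 µm for blood. The criterion is a floor on foveal thickness and says nothing about diameter.

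**3. Effect on endpoint 2.** Let:
- s = share of subjects whose foveal hemorrhage is below 1 disc diameter at baseline (not in the protocol, assumed);
- p = proportion of the other subjects who still have one of at least 1 disc diameter at Week 4 (assumed);
- g = proportion of the initially small bleeds scored as present at Week 4, through growth or a composite-strategy event.

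Observed proportion = p(1 − s) + g·s, so the understatement is s(p − g). With g = 0:

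| s | p = 40%: observed (gap) | p = 60%: observed (gap) |
|---|---|---|
| 10% | 36% (4 points) | 54% (6 points) |
| 20% | 32% (8 points) | 48% (12 points) |
| 40% | 24% (16 points) | 36% (24 points) |

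With g above 0 the gap shrinks. For s = 20%, p = 40% and g = 10%, the observed proportion is 0.40 × 0.80 + 0.10 × 0.20 = 34%, a gap of 6 points rather than 8.

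**4. Per subject, N = 20, g = 0.** Each small bleed adds p/20 to the proportion scored absent: 5 points if no hemorrhage among the other eyes clears (p = 100%), 2.5 points if half clear.

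**5. Effect on the test, illustration only.** The protocol gives no reference value for the chi-square test. With an assumed reference of 50% and N = 20, a favourable significant result needs at least 15 subjects scored absent. If half of the at-risk eyes clear, the chance of this is 2.1% with no small bleeds, and 4.8%, 10.5%, 21.2% and 38.7% with 2, 4, 6 and 8.

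**6. Composite events.** Section 9.1.3 assigns these subjects a value that represents no improvement. For a subject already without a hemorrhage of this extent at baseline, that value is not clear for a present/absent endpoint.

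**The case against.** The strongest case on the other side has five parts.

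- **CFT is a severity gate.** Section 3 says that it reflects the volume of the foveal hemorrhage. This stands. A reader might infer that eligibility ignores hemorrhage size altogether; the documents do not support that. What is missing is lateral extent.
- **The sentence on spontaneous resolution is narrower than it looks.** It speaks of minimal impact on acuity, and the clause about not involving the fovea may qualify both nouns. Every enrolled eye has foveal blood and BCVA of 0.2 or worse. This stands too. A reader might infer that the trial admits exactly the cases on whose exclusion the single-arm design rests; that is arguable and not established.
- **The estimand population is fixed by reference to the inclusion criteria.** The added description can be read as loose wording rather than as a second population. That softens the mismatch, but the description still claims something that the criteria do not select for.
- **Small bleeds may be rare.** Table 6-2 directs the injection into hemorrhage away from the fovea and avoids areas of RPE detachment, and exclusion criterion 15 allows investigator judgement. Nothing in the documents shows that any eye below 1 disc diameter will enrol. This is why s has to be treated as unknown.
- **The SAP could add an at-risk analysis.** It could, and the data will exist. But section 3 of the protocol already fixes the summary measure as a proportion of patients with no baseline condition, so the definition needs correcting there.

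**Conclusion.** The point holds for secondary endpoint 2. As written, its value depends on how many subjects enter with a foveal hemorrhage below 1 disc diameter, which the protocol neither limits nor estimates. The understatement of persistence is s(p − g): 4 to 24 percentage points for s of 10% to 40% and p of 40% to 60%, with small bleeds assumed to stay small and to have no composite-strategy event. These inputs are illustrations, not estimates. If every subject enters at 1 disc diameter or more, there is no bias. The gap also cannot be described as arising with no drug effect, because p may already include one.

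The inconsistency between sections 3, 4.2 and 5.1 is a separate, textual point.

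Two stronger readings are not supported. The primary sample size calculation is not affected. Nor does anything in the documents make 1 disc diameter the mark of a large hematoma: the incidence figure in section 2.2 uses 2 disc diameters. The point therefore gives no basis for a particular eligibility threshold.

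**What to change.** 1. In sections 3 and 9.4.1, define secondary endpoint 2 among subjects with a foveal hemorrhage of at least 1 disc diameter on the screening fundus photograph, and report the number at risk. Alternatively, analyse the paired change in presence from baseline to Week 4. State how a composite-strategy event is scored for a subject without such a hemorrhage at baseline.
2. Reconcile the large-hematoma and at-least-moderate wording of section 4.2, the population descriptions of the three estimands in section 3 and the criteria in section 5.1, so that the no-control rationale and the estimands describe the population that the criteria select. How this is done is for the sponsor; no threshold is proposed here.

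**Cost.** The first change needs no new procedure, because the finding is already assessed at screening under section 8.2.2 and the schedule. Its price is a smaller denominator. With 20 subjects, s of 10%, 20% or 40% leaves 18, 16 or 12 at risk, so the loss is small if few bleeds are small and material if many are. The paired analysis keeps all subjects with both photographs. The second change is an amendment of wording.

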##### <Target Population>

Patients whose underlying disease is AMD or RAM, the principal causes of SMH, will be eligible. Considering the invasiveness and risk of sub-retinal administration, only patients with at least moderate severity will be enrolled: those with a CFT  $\geq 300 \mu\text{m}$  and a BCVA  $\leq 0.2$  (decimal). Patients in whom the clot is organized and unlikely to dissolve, those with concomitant ocular diseases that could affect efficacy or safety assessments, and those at high risk of further bleeding will be excluded.

##### <Evaluation Items>

Central foveal thickness is an objective measurement obtained by OCT, representing the sum of retinal thickness and hematoma volume at the fovea. The therapeutic goal for SMH is to remove the hemorrhage, at minimum from the foveal region, and the thickness of sub-foveal hemorrhage influences visual prognosis. In addition, flattening of hemorrhagic pigment epithelial detachment (PED) has been reported as an effect of intravitreal tPA injection combined with air replacement, and PED flattening may influence the number of additional treatments required and visual prognosis. Considering that this study is exploratory in nature,

CFT, which enables objective evaluation of subfoveal hemorrhage resolution and PED flattening, was selected as the variable for the primary estimand, and the change from baseline was set as the primary endpoint.

#### 4.2.1. Subject Input on Study Design

Not applicable

#### 4.3. Rationale for the Dose

Retinal toxicity has been reported in patients who received intravitreal tPA 50 µg twice consecutively or 100 µg for submacular hemorrhage (SMH). In Japan, reported sub-retinal doses of montepase for SMH secondary to AMD or RAM range from 4,000–32,000 IU (32 µg–256 µg). At the principal site of this trial, Saga University Hospital, off-label use of tPA 5,000–10,000 IU (40 µg–80 µg) has been administered intravitreally or sub-retinally to approximately ten patients per year without safety concerns. Consequently, this trial will employ a dose of 8,000 IU (0.1 mL, tPA 64 µg), which has demonstrated consistent safety and efficacy, as the prescribed dose.

#### 4.4. Definition of Study Completion

The termination of the study is defined as the date of the final assessment of the last subject enrolled in the trial.

Each subject will be considered to have completed the trial upon completion of the 12-week assessment.

### 5. Study Population

No deviations from the eligibility criteria as specified in the clinical trial protocol will be permitted.

#### 5.1. Inclusion Criteria

Subjects are eligible to participate in this trial only if they meet all of the following criteria:

Age:

- 1) Patient aged  $\geq 18$  years at the time of signing the informed consent form.

Disease Characteristics:

- 2) Patient with sub-macular hemorrhage involving the fovea secondary to AMD or RAM in the study eye.

- 3) At screening, CFT measured by OCT in the study eye is  $\geq 300 \mu\text{m}$ .
- 4) At screening, BCVA in the study eye is  $\leq 0.2$  (decimal).

Other:

- 5) Patient who can provide written informed consent; if visual impairment makes document review difficult, verbal consent may be obtained from the subject together with the signature of a witness.
- 6) (For women of child-bearing potential) Patient who, from the time informed consent is obtained until 2 days after investigational product administration, agrees to use an appropriate method of contraception\*.

\* See 10.3.2.

## 5.2. Exclusion Criteria

If a subject meets any one of the following criteria, the subject shall be excluded from the trial:

Condition:

- 1) Patients who, at the time of screening, are judged by the principal investigator or sub-investigator to have had a sub-macular hemorrhage (SMH) for a prolonged period with evident organization or fibrosis.
- 2) Patients who, at the time of screening, have active proliferative diabetic retinopathy, uveitis, or optic neuritis.
- 3) Patients who, in the judgment of the principal investigator or sub-investigator, have ocular comorbidities such as macular atrophy or fibrosis that make visual improvement difficult.

Matters that may affect trial intervention or assessment:

- 4) Patients who, at the time of screening, have anterior-segment or vitreous abnormalities that could interfere with fundus observation by OCT, color fundus photography, or fluorescein angiography.
- 5) Patients with a known allergy to, or a history of allergy to, any component of the investigational product.
- 6) Patients with alcohol dependence, drug dependence, or psychiatric disorders that would interfere with participation in the trial.
- 7) Patients who are scheduled to undergo ophthalmic surgery other than administration of the investigational product during the trial period.

Matters that may affect safety:

- 8) Patients with active bleeding (e.g., gastrointestinal bleeding, urinary-tract bleeding, retroperitoneal bleeding, intracranial hemorrhage, hemoptysis).
- 9) Patients who have undergone intracranial or spinal surgery or have sustained an intracranial or spinal injury within two months prior to obtaining informed consent.
- 10) Patients with intracranial tumors, arteriovenous malformations, or aneurysms.
- 11) Patients younger than 70 years of age with a prothrombin time–international normalized ratio (PT-INR)  $\geq 3.1$ , and patients aged  $\geq 70$  years with PT-INR  $\geq 2.7$  (unless it is anticipated that the INR can be reduced below these levels before vitreous surgery, taking into account the balance between systemic risk and intra-ocular hemorrhage risk; in such cases, PT-INR  $< 2.7$  must be confirmed by laboratory testing on the day of surgery).
- 12) Patients with hypertension whose systolic blood pressure remains  $\geq 180$  mmHg despite antihypertensive therapy.
- 13) Women of child-bearing potential who are not using adequate contraception, pregnant women, women who may be pregnant, lactating women, or subjects who plan to become pregnant during the trial period.

Other:

- 14) Patients currently participating in another clinical trial, or who have participated in another trial within six months prior to obtaining informed consent.
- 15) Patients deemed unsuitable by the principal investigator or sub-investigator.

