#### 1.3. Schedule of Activities (SoA)

| Activity                                     | Consent         | Screening             | Enrollment | Treatment period                 |                |                |                |                | Observation period |                 |                 |                 |                 | Discontinuation    |
|----------------------------------------------|-----------------|-----------------------------------|------------|----------------------------------|----------------|----------------|----------------|----------------|--------------------|-----------------|-----------------|-----------------|-----------------|--------------------------------|
| Visit                                        |                 |                                   |            | Visit 1                          | Visit 2        | Visit 3        | Visit 4        | Visit 5        | Visit 6            | Visit 7         | Visit 8         | Visit 9         | Visit 10        |                                |
| Week                                         |                 | Within 7 days before registration |            | 0                                |                |                |                | 1              | 2                  | 3               | 4               | 8               | 12              |                                |
| Day                                          |                 |                                   |            | 1                                | 2              | 3              | 4              | 8              | 15                 | 22              | 29              | 57              | 85              |                                |
| Visit window (Day)                           |                 |                                   |            | Within 7 days after registration | —              | —              | —              | -1~+3          | $\pm 3$            | $\pm 3$         | $\pm 3$         | $\pm 7$         | $\pm 7$         | +7                             |
| Intervention                                 |                 |                                   |            | ○                                |                |                |                |                |                    |                 |                 |                 |                 |                                |

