| Chest X-ray                                  |                 | ○                     |            |                                  |                |                |                |                |                    |                 |                 |                 |                 |                                |
| Electrocardiogram                            |                 | ○                     |            |                                  |                |                |                |                |                    |                 |                 |                 |                 |                                |
| Concomitant medications / therapies          |                 |                                   |            |                                  |                |                |                |                |                    |                 |                 |                 |                 |                                |
| Adverse events                               |                 |                                   |            |                                  |                |                |                |                |                    |                 |                 |                 |                 |                                |

\*1 If a partner medical institution is not available, the clinical trial site shall be visited.

\*2 Either the partner medical institution or the trial site may be used. When multiple test results are available within the period, the data closest to the enrollment date shall be used.

\*3 If data are available within 7 days after enrollment, they may be used even before consent acquisition.

\*4 Measured before and after dosing.

\*5 Performed only on the treated eye.

\*6 May be performed at the trial site or at the partner site. If performed at the partner site, the trial site will provide remote medical care.

\*7 Performed only if discontinuation occurs before Visit 3.

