#### 6.3. Allocation of Trial Intervention

The principal investigator or sub-investigator shall, after obtaining written informed consent from the patient, confirm that all inclusion criteria are met and that none of the exclusion criteria apply. Thereafter, the principal investigator, sub-investigator, or clinical research coordinator will perform registration using an electronic data capture (EDC) system. All registered subjects will be assigned to the active-drug group.

[EDC System]

Fountainyn

Registration hours: 24-hour registration possible (excluding maintenance/inspection periods)

Contact: Kyushu University Hospital ARO Next-Generation Medical Center, Clinical Research Management Division, Data Science Office

Weekdays 9:00 – 17:00 (excluding Saturdays, Sundays, public holidays, and the year-end/New-Year period (12/29 – 1/3))

Precautions for registration:

- ✓ Registration after administration of montepase (recombinant) is not permitted under any circumstances.
- ✓ In the EDC system, registration will not be accepted until all required input fields are completed.
- ✓ Registration is considered complete when eligibility is confirmed and a registration number is issued.
- ✓ Except when a subject withdraws consent, including refusal to allow data use, a subject once registered will not have that registration cancelled. In the event of duplicate registration, the information from the first registration (including registration number) will be used.
- ✓ If erroneous or duplicate registration is discovered, the data-management staff must be notified promptly.

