#### 8.3.2. Laboratory Blood Tests

The following parameters shall be measured.

[Hematology] Red blood cell count, hemoglobin, hematocrit, white blood cell count, differential white blood cell count (neutrophils, lymphocytes, monocytes, eosinophils, basophils), platelet count

[Clinical Chemistry] Albumin, total bilirubin, direct bilirubin, AST, ALT, alkaline phosphatase, LDH,  $\gamma$ -GTP, BUN, creatinine, CRP, sodium, potassium, chloride, calcium, glucose (as needed)

[Coagulation] PT-INR, APTT, fibrinogen, D-dimer

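### Exclusion 11 requires a same-day PT-INR only for patients entering under its exception; other subjects on an INR-affecting anticoagulant can be dosed on a result up to 14 days old

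*Protocol*

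**What the plan says.** - **Limit and exception (Protocol 5.2, item 11).** Under 70 years, a PT-INR of 3.1 or more excludes; at 70 or over, 2.7 or more excludes. The exclusion is lifted where the INR can be expected to fall in time: "unless it is anticipated that the INR can be reduced below these levels before vitreous surgery". For patients admitted that way, a value below 2.7 "must be confirmed by laboratory testing on the day of surgery". Item 11 stands among the criteria concerned with safety.
- **When eligibility is checked (6.3).** Before registering a patient the investigator must "confirm that all inclusion criteria are met and that none of the exclusion criteria apply". The same section adds: "Registration is considered complete when eligibility is confirmed and a registration number is issued".
- **Windows (1.3).** Screening: "Within 7 days before registration". Visit 1, the day of surgery and dosing: "Within 7 days after registration". If several screening results exist, footnote 2 takes the one nearest to enrollment.
- **When INR is measured (1.3 and 8.3.2).** The coagulation part of the blood test is "PT-INR, APTT, fibrinogen, D-dimer". The blood-test row is marked at screening and at Visit 3 (Day 3). Footnote 7, on the blood test at discontinuation, reads: "Performed only if discontinuation occurs before Visit 3".
- **Anticoagulants.** Section 6.9.2.2 permits them.

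**The concern.** The purpose of item 11 is to limit bleeding risk when a thrombolytic is injected during vitreous surgery, so the INR that matters is the one at the time of injection. The protocol accepts this for exception entrants, for whom it demands a same-day result. It makes no such demand for a subject who was under the limit at screening but takes an anticoagulant that affects PT-INR. That subject may be close to the limit, and the INR may change before surgery. A rise above the limit need not cause symptoms, so without a required test it can go unnoticed until after the drug is in the eye. What is at stake is the safety of a few subjects, not the efficacy estimate.

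**Working it through.** **Inputs**

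| Input | Value | Source |
|---|---|---|
| Screening window | up to 7 days before registration | 1.3 |
| Visit 1 window | up to 7 days after registration | 1.3 |
| Day of dosing | Day 1 | 1.3 |
| Next scheduled blood test | Visit 3, Day 3 | 1.3 |
| Limit, under 70 | PT-INR below 3.1 | 5.2, item 11 |
| Limit, 70 or over | PT-INR below 2.7 | 5.2, item 11 |
| Same-day limit, exception entrants | PT-INR below 2.7 at any age | 5.2, item 11 |

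The protocol states no figure for the age of the INR at dosing, so there is none to reproduce.

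**Step 1. Age of the INR at dosing**
- Oldest = screening window + Visit 1 window = 7 + 7 = 14 days. Youngest = 0 days.
- Dosing to next scheduled INR = Day 3 − Day 1 = 2 days.
- Longest gap between two scheduled INRs with dosing in between = 7 + 7 + 2 = 16 days.

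**Step 2. What each kind of subject must show before dosing**

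| Age | Screening INR | INR on the day | Required same-day test? | Result |
|---|---|---|---|---|
| 75 | 2.6 | 2.8 | No | Above the limit of 2.7; no required test would detect it |
| 75 | 2.8 (exception) | 2.8 | Yes | Not dosed |
| 75 | 2.8 (exception) | 2.6 | Yes | Dosed |
| 65 | 2.8 | 3.0 | No | Below the limit of 3.1; may be dosed |
| 65 | 3.2 (exception) | 2.8 | Yes | Not dosed |
| 65 | 3.2 (exception) | 2.6 | Yes | Dosed |

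The first row is the gap. An under-70 below 3.1 at screening who rises to 3.1 or more is in the same position.

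**Step 3. Do other provisions close it?**
- Section 8 allows off-schedule assessments for safety reasons but does not require them.
- Section 7.1 stops the intervention before surgery if the subject's systemic condition has worsened too far. It names no test.
- Section 7.2, item 2, discontinues a subject found to be ineligible after enrollment. It applies only once someone has looked.

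None of the three requires an INR.

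**Step 4. Exception wording for under-70s**
- Level the INR must be expected to fall below: 3.1. Level required on the day: 2.7. Difference = 3.1 − 2.7 = 0.4 INR units.
- At 70 or over: 2.7 − 2.7 = 0.
- Any value below 2.7 is also below 3.1, so both conditions can be met together.

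**The case against.** The best defence is that same-day testing has been placed where the known risk lies: in patients already over the limit. The sites must have experience with sub-retinal tPA, subjects are in hospital at Visit 1, re-testing is allowed, and prompt removal of the hemorrhage is the treatment goal (2.2), so a 14-day interval should be unusual. All of this stands and keeps the point small. It does not replace a required test.

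Three stronger readings are tempting, and the document does not support them.

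- **That no INR limit applies at dosing to ordinary entrants.** Several other criteria are tied to screening in so many words; item 11 is not. Section 5 allows no deviation from the eligibility criteria, and 7.2 covers a subject later found ineligible. Item 11 can therefore be read as applying up to surgery, although 6.3 places the check before registration. What is missing is a required test, not the limit.
- **That the exception contradicts itself for under-70s.** It does not, as Step 4 shows. The stricter level decides whether the drug is given, so the mismatch fails on the safe side. The worst result is an under-70 who is registered and then not dosed. A tighter level for patients known to have been over the limit may be a deliberate margin.
- **That the blank Day 1 cell in the blood-test row removes the test for exception entrants.** Item 11 itself mandates that test, so the missing mark is editorial. The table has also come through extraction imperfectly, and its layout should not carry much weight. Footnote 7 supports Visit 3 as a scheduled blood test but cannot by itself rule out one on Day 1. The main point does not rest on the blank cell alone: no text elsewhere in the protocol requires a pre-dose INR from ordinary entrants.

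**Conclusion.** The point holds as a minor safety gap. A subject on an INR-affecting anticoagulant who was under the item 11 limit at screening can receive sub-retinal tPA on a result 0 to 14 days old, and no provision obliges the site to learn that the INR has since passed the limit.

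This assumes that the blood-test row is marked at screening and Visit 3 only, as it reads here, and that INR can change within the window in such subjects, which is clinical judgement and not a figure in the protocol. The protocol gives no INR distribution, age distribution or share of subjects on anticoagulants, so the number affected cannot be stated; among 20 subjects it is probably small. The sample size and primary analysis are unaffected. The wording difference for under-70s is worth tidying but is not an error.

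**What to change.** 1. **Item 11.** Add that for every subject taking an anticoagulant that affects PT-INR, PT-INR is measured on the day of surgery before administration. The product is given only if the result is below 3.1 (under 70 years) or below 2.7 (70 or over). For exception entrants the level stays below 2.7 at any age, as already stated.
2. **If the result is not below the limit.** Postpone within the Visit 1 window, which ends 7 days after registration. If it is still not below, do not dose.
3. **Schedule (1.3).** Add a Day 1 footnote for this test, covering exception entrants as well.
4. **Optional clarification.** State the exception's expected level as below 2.7, so that it matches the level needed on the day.

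Under this change an under-70 at, say, 2.8 on the day would still be dosed by the ordinary route and refused by the exception route. If that margin is intended, a short reason in item 11 would help sites.

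The cost is one amendment to item 11, one schedule footnote, one extra coagulation test in a few subjects already in hospital on Day 1, and an occasional postponed operation. For the subjects tested, the oldest INR relied on at dosing falls from 14 days to the same day.
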